### Randomisation and allocation

First, participants will be stratified into Christian and Islamic samples. They will then be randomly assigned to the spiritual meditation (either Christian or Islamic meditation, with religious affiliation restricting allocation to either the Christian or Islamic type of contemplation), MBSR, or waitlist control, utilizing a random number generator produced by a computer and allocated to one of the four groups. To ensure allocation concealment, the allocation process will be carried out by a researcher who is independent of the trial team.

### Blinding

Neither the participants nor assessors can be completely blinded given that it is not possible to create a pseudo-Christian or Islamic meditation condition. To reduce potential biases, participants will be blind to the specific study hypotheses, and will only have access to the meditation app version exclusively for their assigned groups. Additionally, the researcher responsible for the randomisation and allocation process will not participate in the recruitment, assessment, or data analysis. Considering that the trial will not involve any harmful procedure, and participants will be informed about the three arms during the recruitment stage, procedure for unblinding is not required for this trial.

### Study interventions

The spiritual meditation interventions and MBSR will have the same structure and time frame. All interventions will be delivered through an initial face-to-face meeting, where participants will initiate the first session of the guided meditation course using the mobile app. Subsequently, they will continue with daily guided practices lasting approximately 20 min through the app over eight weeks. The initial meeting will start at the end of the baseline assessment (T1). Participants will only be able to access the app intervention that they are allocated to. Participants in the waitlist control group will not receive any types of intervention and will not attend the T3 assessment, but they will be given access to the Christian or Islamic meditation app version upon completion of the in-person T2 assessment.

### Intervention content

All interventions will be delivered through an 8-week program of daily audio-guided meditations of approximately 20-minutes. There will be a total of eight different meditations per condition, one per week, where each meditation is repeated across seven days. To ensure participant engagement in the meditation practice, the app will unlock the next session for the participant only after completing the preceding day’s session. Similarly, progression to the next week’s meditation session requires completing at least four sessions in the preceding week. The app will track participants’ completion of practice sessions and record daily responses to two brief questions about mood and meditation experience. Participants can maintain their daily religious practices during the 8-week program.

### Heart-centred spiritual meditations

The spiritual meditation programs were developed from techniques based on Christian and Islamic traditions. The primary elements of the practices consist of maintaining attention and emotional connection to God through visualisation and recitation. Concurrently these practices are expected to promote a moving away or transcendence from everyday concerns. Breathing is included as an added ingredient to help focus participants’ attention during the first part of each meditation. Although Christian and Islamic contemplations are typically not standardised within their respective contemplative traditions, for this study we had to develop specific scripts to be used by participants. These were developed by Christian and Islamic expert members of the research team, and subsequently edited by the lead researchers with the guidance of an expert in writing content for meditation Apps (see acknowledgements section).

### Mindfulness-based stress reduction

A separate MBSR program was developed by a certified instructor who has experience in working for meditation Apps. The MBSR program includes an 8-week program of daily audio-guided mindfulness practice lasting approximately 20 min, based on the manual developed by John Kabat-Zinn [44]. 

### Waitlist condition

Participants assigned to the waitlist control condition will take part in the assessments at T1 and T2 but will not participate in any of the interventions. They will be given access to either the Christian or Islamic spiritual meditation app version after they complete the assessment at T2.

### Study variables

Table 2 provides a summary of the variable domains, study variables, measures, assessment time points and the types of data collection method for each variable.

**Table 2 Tab2:** Overview of the outcome measures and points of assessment

Domain	Variables	Measure	Type of data collection method	Assessment point			
				Pre-intervention (T1)	Post-intervention (T2)	At 3-month follow-up (T3)	Throughout the 8-week intervention
Primary outcome measures							
Interpersonal functioning	Prosociality	Dictator Game: number of points (0–10) that a participant is willing to allocate to another individual.	Lab	X	X		
	Prosociality	Social value orientation task	Online	X	X		
	Prosociality	Charitable Giving: percentage of monetary compensation donated to a charity.	Lab		X		
	Forgiveness	Forgiveness scale assessed as part of Love thy Enemy task	Lab	X	X		
	Empathy	Empathy scale assessed as part of Love thy Enemy task	Lab	X	X		
	Perspective Taking	Interpersonal Reactivity Index (IRI)	Online	X	X	X	
Secondary Outcome measures							
Physiology	Pain Tolerance	Endurance (in seconds) of cold painful stimulation	Lab	X	X		
	Pain Intensity	0–10 Rating Scale	Lab	X	X		
	Stress Reactivity	HR	Lab	X	X		
	Stress Reactivity	HRV	Lab	X	X		
	Psychophysiological reactivity associated with forgiveness	HR assessed during forgiveness task.	Lab	X	X		
	Psychophysiological reactivity associated with forgiveness	HRV assessed during forgiveness task	Lab	X	X		
Attention	Alerting Attention network	Reaction times assessed through a 10-minute version of the Attention Network Task (CRSD-ANT)	Lab	X	X		
	Orienting Attention network	Reaction times assessed through the (CRSD-ANT)	Lab	X	X		
	Executive Attention network	Reaction times assessed through the CRSD-ANT	Lab	X	X		
Mental health	Stress	Stress subscale of the Depression, Anxiety and Stress Scale (DASS-21)	Online	X	X	X	
	Depression	Depression subscale of the DASS-21	Online	X	X	X	
	Anxiety	Anxiety subscale of the DASS-21	Online	X	X	X	
	Subjective Wellbeing	Well-Being Index (WHO-5)	Online	X	X	X	
	Positive and Negative Affect	Positive and Negative Affect Schedule (PANAS) Short Form (I-PANAS-SF)	Online	X	X	X	
	Positive and Negative Affect	Smiley Face Likert scale	Phone App				X
Other variables							
Spirituality	Spiritual experiences	16-item Daily Spiritual Experience Scale	Online	X	X	X	
	Closeness to God/Inclusion-of-God-in-the-self	Pictorial closeness to God / Inclusion-of-God-in-the-self	Online	X	X	X	
	Religiosity	5-item Duke University Religiosity Index	Online	X			
	Credibility/expectancy of the meditation practices	2-item scale	Online	X			
	Meditation adverse events	Self-report scale on meditation unpleasant events and harm	Online		X	X	
	Closeness to the offender	Pictorial Inclusions of Others in the Self scale with the Love thy Enemy task	Online	X			
Other	Age	Self-report	Online	X			
	Ethnicity	Self-report	Online	X			
	Gender identity	Self-report	Online	X			
	Sex	Self-report	Online	X			
	Employment status	Self-report	Online	X			
	Education level	Self-report	Online	X			
	Annual household income	Self-report	Online	X			
	Experiences of the App-based exercises	Self-report	Online		X	X	
	Frequency of the contemplative or mindfulness practices after the end of the intervention	Self-report	Online			X	
	Qualitative assessment (Paper diary)	Themes emerging from participant’s meditation experiences					X
	Qualitative assessment (App)	Themes emerging from participant’s daily meditative experiences					X

### Primary outcomes

The study is primarily assessing changes in interpersonal functioning, measured through prosociality, forgiveness, empathy, and perspective taking. Prosociality will be assessed at T1 and T2 via the *Dictator Game* (DG) [45], *Social Value Orientation* (SVO) [46], and *Charitable Giving* (at T2 only). Empathy and forgiveness variables will be collected via the task *Love thy Enemy* (adapted from Witvliet et al. [47]) at both T1 and T2. Perspective taking will be obtained online at T1, T2, and T3.

Dictator Game (DG) [45]: This computer-based task allocates ten game points to participants and asks them to decide how many of these points they would like to transfer to an anonymous participant. The outcome measure is the number of game points participants are willing to allocate to the anonymous individual. The game points retained by participants will have no influence on their real-life earnings or their compensation fee for taking part in the experiment. Prior studies have shown that individuals engage in prosocial activities irrespective of monetary incentives [48, 49]. 

Social Value Orientation (SVO) [46]: This online task consists of six items with which participants are asked to assign game points for themselves and an anonymous other. Participants will make their allocations by adjusting a slider to indicate their most preferred joint distribution between themselves and the other. A continuous social value orientation score will be computed from these six items based on participants’ choices. The outcome measure will be a single overall SVO score. A higher SVO score represents a higher prosocial preference. The game points kept by the participants will not affect their real-life earnings or their compensation fee for taking part in the experiment.

#### Charitable giving

Participants will be given a choice to allocate a part of their compensation fee to a charity (ranging from 0 to 100%). The prosocial outcome measure will be the percentage of the fee they are willing to allocate to a charity (Christian or Islamic, based on the participant’s religious affiliation).

Love thy enemy task (adapted from Witvliet et al. [47]): In this forgiveness task participants will focus on an enemy who has deeply hurt them; self-reported empathy and forgiveness are assessed, alongside HR and HRV to measure psychophysiological reactivity associated with forgiving the offending individual. Participants will first be asked to think of an individual who has deeply hurt them. They will then write down the initials of that person’s name, as well as when and where the specific incident happened on a piece of paper, which they will subsequently seal in an envelope (the envelop will remain sealed until T2, when participants will be asked to recall the same individual and incident). After writing down this information, participants will indicate the level of closeness they feel towards that individual (adapted from Aron et al. [50]). Once participants indicate the relationship with the person, they will proceed to the task, which consists of three phases: baseline, imagery, and recovery. In the baseline and recovery phrases (20 s for each), participants will be instructed to close their eyes and relax. In the imagery phase (40 s of duration) participants will be prompted to imagine themselves forgiving the person who hurt them. After the recovery phase, participants will rate their level of empathy towards that person (on a scale of 0–20) and the extent to which they feel they have forgiven the person during the task (on a scale of 0–20). The task will consist of four repeated trials.

Perspective Taking [51]: The 7-item Perspective Taking subscale from the Interpersonal Reactivity Index (IRI) will be used to assess participants’ tendency to take others’ points of view using a 5-point Likert scale, ranging from A (Does not describe me well) to E (Describes me very well). Higher scores indicate greater perspective-taking.

### Secondary outcomes

Secondary outcomes encompass domains of physiology, attention, and mental health. Measures pertaining to the physiological and attention domains will be obtained at T1 and T2, while those related to mental health domain will be collected across all timepoints (T1, T2 and T3).

### Physiological domain

Pain tolerance, pain intensity, and stress reactivity (HR and HRV) will be assessed using a cold pressor task (adapted from a previous spiritual intervention study [52]). Participants will immerse their non-dominant hand in the cold water at 2 °C to 3 °C. They will be instructed to endure the pain for as long as they can tolerate, up to a maximum of 4 min, with an option to remove it any time if the pain becomes unbearable. HR and HRV will be continuously measured throughout the task. After removing their hand from the cold water, participants will rate their average pain intensity experienced during the task ranging from 0 (no pain) to 10 (worst imaginable pain). A 5-minute resting state HR and HRV will be measured before the task, with another 5-minute HR and HRV measurement starting 1 min after the end of the cold pressor task. Custom computer software will record the duration (in seconds) that a participant endures painful stimulation during the cold pressor task as well as HR and HRV. The four variables assessed include (1) the duration of cold-water endurance (pain tolerance), (2) differences in HR and HRV before, during and after the task (stress reactivity), and (3) the average subjective pain intensity.

For HR and HRV measurement, participants will wear a Polar H10 heart rate sensor [53] around their chest to measure HR and interbeat intervals for quantifying the metric of root mean square of successive RR interval differences (RMSSD) for HRV. A software program has been customized to interface with the modified version of the OpenHRV application [54]. 

### Attention domain

Posner and Petersen [55] identified three distinct networks linked to different aspects of attention: one for alerting, involving right frontal and parietal regions; another for orienting with frontal and parietal lobe involvement; and a third for executive control linked to the anterior cingulate and dorsolateral prefrontal cortex. The Attention Network Task (ANT) was designed to assess the efficiency of each network through behavioural data [56]. This study uses the 10-minute version of the ANT (adapted from the attention network task) [56, 57]. 

Throughout the task, a fixation cross will be presented in the centre of the screen. Brief cue stimuli, lasting for 100ms, will appear above or below the fixation cross (spatial cue), with two cues - one above and the other below the fixation cross (double cue), at the centre of the fixation cross (centre cue), or not at all (no cue). These cues will consistently precede the target presentation. Centre and double cues provide timing information regarding when the target will appear, concerning alerting attention, while spatial cues also indicate where the upcoming target would be, involving orienting network. The target stimuli consist of five horizontally arranged arrows, positioned above or below the fixation cross, with a maximum duration of 1500ms. Participants are instructed to press the left or right arrow key on their keyboard to indicate the direction of the central arrow, regardless of the flanking conditions, with all arrows either pointing in the same direction (congruent flankers) or pointing in different direction from the central arrows (incongruent flanks). Reaction time (RT) difference across task conditions serve as outcome measures, which reflect the engagement of corresponding attention network, with a faster RT indicating a greater alerting, orienting, or executive control of attention, depending on the task type.

#### Mental health domain

This domain includes measures of stress, depression, anxiety, subjective welling, and positive and negative affect.

Stress, depression, and anxiety: These variables will be assessed using the 21-item Depression, Anxiety and Stress Scale (DASS-21) [58]. Previous research has indicated that the DASS-21 exhibits comparable levels of internal consistency across various cultures and countries [59, 60]. The scale comprises three subscales: depression, anxiety, and stress, each comprising seven items. Participants will rate how they feel over the preceding week using a 4-point Likert scale ranging from 0 to 3, where 0 indicates “Did not apply to me at all” and 3 represents “Applied to me very much or most of the time”. Total subscale scores will be computed by summing all item responses, with higher scores indicating greater symptom severity.

Subjective well-being (WHO-5) [61]: The WHO-5 comprises five items that requires participants to assess their feelings over the preceding two weeks using a 6-item Likert scale ranging from 0 to 5, where 0 represents “At no time” and 5 indicates “All of the time”. A higher score indicates a greater sense of wellbeing.

Positive and negative affect (I-PANAS-SF) [62]: This consists of a 10-item scale with higher scores indicating greater positive or negative affect.

##### Mood

A 1-item Smiley Face Likert scale within the meditation app will ask participants to assess how they are currently feeling before and after each meditation or mindfulness session. Participants select one of the five emoji faces, arranging from very sad (leftmost) to very happy (rightmost).

### Other variables

Other variables include spirituality domain related to measures of spiritual experiences, closeness to God, religiosity, demographics, socioeconomic status, and control variables.

#### Spirituality domain

##### Spiritual experiences

Spiritual experiences will be measured using the 16-item Daily Spiritual Experience Scale (DSES) [63]. Participants will rate the frequency of specific spiritual experiences using a Likert scale. While one item employs a 4-point Likert scale, with a higher score representing greater spiritual experiences, the remaining 15 items are measured on a 6-point Likert scale and are reverse-scored, with lower scores signifying greater spiritual experiences. This assessment will be conducted across all time points (T1, T2, and T3).

##### Closeness to god/inclusion-of-god-in-the-self

The measurement will employ a pictorial inclusion of God scale adapted from the Inclusions of Others in the Self scale (IOS) [50], specifically tailored to assess closeness to God. The scale comprises seven pairs of circles with varying degrees of overlap, describing the relationship between oneself and God. Greater overlap signifies a closer relationship with God, while less overlap indicates a more distant relationship. This measure will be collected across all time points (T1, T2, and T3).

##### Religiosity

It will be assessed at T1 using the 5-item Duke University Religiosity Index (DUREL) [64], measuring three primary dimensions of religious involvement: organizational religious activity (ORA) and non-organizational religious activity (NORA), and intrinsic religiosity (IR). Participants rate their involvement (ORA and NORA) on a 6-point Likert scale ranging from 1 (Never) to 6 (More than once a week) for two items, and their religious beliefs or experiences (IR) on a 5-point Likert scale ranging from 1 (Definitely not true) to 5 (Definitely true of me). Higher scores indicate a stronger religiosity.

#### Control variables

##### Credibility/expectancy of the meditation practices

A modified version of the 2-item self-report questionnaire (adapted from Creswell et al. [65]) will be used to assess participants’ belief about the relevance and the efficacy of the meditation and mindfulness interventions at T1. Higher scores indicate greater positive expectancies.

Potential adverse events (adapted from Baer et al. [66]): This questionnaire assesses unpleasant experiences and potential harm from the meditation practices and includes items with Likert. It will be used at T2 and T3.

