## Participants

### Power analysis

This study will recruit non-clinical samples of 144 Christian and 144 Islamic healthy adult participants. An a priori power analysis was conducted using the G*Power software (V.3.1) [42], considering four groups with mixed method repeated measures at three timepoints. The calculation was conducted based on a small effect size of *f*^*2*^ = 0.1, with an alpha value of 0.05, a desired power of β = 0.85. Effect size was set at 0.1 using a conservative approach due to the novel nature of the study to examine the effects of Christian and Islamic contemplation. Calculation was applied to determine the total sample size of 288 participants with (*n* = 72) per group, after adjusting for an estimated dropout rate of 10%.

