## Adverse events and safety monitor

We have established an expert panel to guide the study’s design and intervention. Additionally, a dedicated study coordinator oversees the logistical and operational aspects of our research. Given that the potential for adverse events linked to meditation practices [67], we will assess this risk by including a self-report measure for adverse events. Participants will be also asked to reflect on their experiences during the practices. To address concerns, participants can consult religious experts from our advisory board regarding any potential adverse effects of the interventions. They will also be encouraged to promptly contact the lead researcher if adverse events occur, as outlined in the participant information sheet.

Participants undergoing the cold pressor task procedures may experience discomfort or pain, inherent to the procedure’s design. They will be informed that they have the option to discontinue the procedure and remove their hand from the cold water at any time. The cold pressor task is a well-established procedure, and unexpected adverse effects related to the cold pressor task procedure are unlikely to occur. Therefore, based on our risk assessment and the low anticipated risk, a formal data monitoring committee and modifications of allocated intervention are considered unnecessary for this study. It is also unlikely that participants will require post-trial care. However, the lead researcher will closely monitor and document any potential adverse events. Participants will be informed of their right to withdraw from the trial at any time without needing to provide a reason.

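### The only structured harm questionnaire is given at T2 and T3, so people who withdraw before T2 do not complete it and its harm rates are conditional on staying

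*Protocol article*

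**What the plan says.** Under Control variables, the article describes the adverse-event instrument: "This questionnaire assesses unpleasant experiences and potential harm from the meditation practices". Its timing follows: "It will be used at T2 and T3". Table 2 (Study variables) lists it as "Self-report scale on meditation unpleasant events and harm", collected online and marked at T2 and T3. That table also has a column for collection throughout the eight weeks. The app mood rating, the diary and the app text are marked there; the harm scale is not.

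The section Adverse events and safety monitor presents a self-report measure as the means of assessing the risk of adverse events from meditation. It tells participants of their "right to withdraw from the trial at any time without needing to provide a reason", and it considers a formal data monitoring committee unnecessary. The section on interim analyses plans none and sets no stopping guidelines.

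Other routes for capturing harm are described:
- The diary (Qualitative measure) is kept during the eight weeks, and one of its stated purposes is to evaluate potential adverse events.
- The app asks for feedback after each session, mainly on mood, emotions and how effective the session was. A mood rating is taken before and after each session.
- Participants are encouraged to report adverse events to the lead researcher, who is to monitor and document them.

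The recruitment section invites all enrolled participants to T2. Under Power analysis, the sample size was fixed "after adjusting for an estimated dropout rate of 10" per cent.

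**The concern.** The questionnaire is the only instrument that puts the same harm questions to everyone, so it is the natural source of a harm rate for each programme. Because it is first given at T2, a person who leaves the trial in, say, week 2 has gone before it is due. If unpleasant experience is one reason for leaving, those most likely to report harm are under-represented among those who answer.

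The spiritual programmes were scripted for this study, so how well they are tolerated is a real question. A low questionnaire-based rate could be read as the rate among all who started, when it describes only those who stayed. If withdrawal for unpleasant experiences differed between the spiritual and mindfulness apps, rates set side by side would not be comparable either.

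**Working it through.** **The plan's own figure.** Power analysis gives 72 per group in four groups: 4 × 72 = 288, matching 144 + 144. A repeated-measures calculation for the group-by-time interaction (four groups, three time points, alpha 0.05, power 0.85, effect size f = 0.1) gives 260 evaluable participants. This assumes a correlation of 0.5 between time points and sphericity, neither of which the article states. Then 260 / 0.9 = 289, against the stated 288. The total and the 10% allowance are therefore coherent and can be used below. (The article prints 0.1 as f²; 288 is reproduced only if it is f. That does not affect this point.)

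**How many could be missed.** Inputs are 288 participants and 10% dropout (Power analysis). The article describes both three conditions and four groups, so the number given an app depends on the split:
- Three equal arms of 96, two with an app: 2 × 96 = 192; 0.10 × 192 = 19.2, about 19.
- Four groups of 72, three with an app: 3 × 72 = 216; 0.10 × 216 = 21.6, about 22.

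These are upper limits under the planned dropout. The 10% has no stated timing or arm, and the calculation covers three time points, so some of the loss may fall between T2 and T3, after the form has been given once.

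**What the other routes record for someone who withdraws before T2.**

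| Source | Before T2? | Structured on harm? | Limit |
|---|---|---|---|
| Questionnaire | No | Yes | First given at T2 |
| Diary | Yes | No | Thematic analysis; recovery from leavers not described |
| App feedback and mood rating | Yes | No | Tied to sessions, so ends when practice ends; not harm-specific |
| Contact with lead researcher | Yes | No | Begun by the participant |

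The leaver may already have left diary or app entries, but nothing that can be tabulated as a harm rate by arm alongside the questionnaire.

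**Illustration of the bias.** The article gives no harm rates, so all rates here are assumptions. Take 216 app users, 22 leavers before T2 and 194 stayers, with 5% of stayers reporting harm. If a share s of leavers would have reported harm:

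rate in all = (0.05 × 194 + s × 22) / 216

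| s | Rate in all | Questionnaire rate | Understatement, 1 − 5 / rate in all |
|---|---|---|---|
| 0% | 4.49% | 5% | none (overstated) |
| 5% | 5.00% | 5% | none |
| 10% | 5.51% | 5% | 9% |
| 20% | 6.53% | 5% | 23% |
| 30% | 7.55% | 5% | 34% |

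With 192 app users (19 leavers, 173 stayers) and s = 20%: (8.65 + 3.8) / 192 = 6.48%, again an understatement of about 23%.

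**If no events were reported.** With none in 194 stayers, the one-sided 95% upper bound is 1 − 0.05^(1/194) = 1.5%. That bound applies to stayers only, while up to 22 of 216 (about 10%) would not have completed the form.

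**The case against.** The strongest reply is that harm capture does not wait for T2. The diary is partly meant to detect adverse events, the app collects feedback after every session, and the lead researcher documents what is reported. A person who leaves in week 2 may already have two weeks of entries on record. This stands. A reader might infer that harm is counted only among those who stayed, or that leavers are never asked about their experience; the article does not support either. What these routes lack is a common set of harm questions that yields a rate.

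A reader might also infer that people who merely stop practising are missed. They are not: every enrolled participant is invited to T2, with no condition on practice, and the harm form is online. Only withdrawal from the trial before T2 creates the gap.

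It can further be said that a journal article condenses the full protocol, which may contain an exit procedure. If it does, the point falls away. But the article does more than stay silent: it fixes the timing of the form in two places that agree, and neither includes withdrawal.

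Finally, adverse events are not listed as a primary or secondary outcome, and the analysis plan announces no comparison of harm between arms. That limits the consequence: a biased comparison would arise only if rates were set side by side. It does not change what a reported rate would mean.

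**Conclusion.** The point holds in limited form. As written, the only structured harm measure is not completed by anyone who withdraws before T2, so harm rates from it describe those who stayed. At most about 19 of 192 or 22 of 216 app users are affected, and only if the whole planned 10% dropout falls before T2.

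Downward bias is conditional. It arises if harm is more common among leavers than among stayers; with equal rates there is none, and with lower rates among leavers the questionnaire rate is too high. The 9% to 34% understatement shows scale under assumed rates and is not an estimate for this trial. Nothing here affects the efficacy outcomes or the sample size.

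**What to change.** Offer the existing online questionnaire, optional to answer, when a participant withdraws. No change is needed for those who stop practising but remain enrolled, since T2 already covers them.

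Report harms by arm and by source (questionnaire, diary or app text, spontaneous report), with everyone randomised to each app as the denominator. Show for each arm how many did not answer the questionnaire, so that the rate is not read as covering people it did not reach.

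The cost is one extra trigger for a form that already exists and a line in the participant information. The downside is a small burden on leavers, who may decline; their right to leave without giving a reason is untouched.
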